## Abstract

**Introduction:**

Millions of women suffer from the consequences of endometriosis and uterine fibroids, with fibroids the cause for over 50% of hysterectomies in the USA, and direct costs for their treatment estimated at between US$4 and US$9 billion. Endometriosis commonly affects millions of women worldwide predominantly during reproductive age, with severe menstrual and non-menstrual pain and subfertility the main symptoms. Due to the ‘unhappy triad’ of endometriosis—lack of awareness, lack of clinically relevant biomarkers and the unspecific nature of symptoms—women wait on average for 8–12 years before the definitive endometriosis diagnosis is made. Treatment options for both conditions are not satisfactory at the moment, especially with a view to preserving fertility for the women and families affected. In the Fibroids and Endometriosis Oxford (FENOX) study, we combine the investigation of fibroids and endometriosis, and plan to collect high-quality tissue samples and medical data of participants over a time frame of 5 years after surgical intervention.

**Methods and analysis:**

Biological samples such as blood, saliva, urine, fat, peritoneal fluid and—if found—endometrial tissue or fibroids as well as detailed clinical and intraoperative data will be collected from women undergoing surgery and participating in the study after informed consent. We plan to recruit up to 1200 participants per disease arm (ie, endometriosis and uterine fibroids) over 5 years. Participants will fill in detailed and validated questionnaires on their medical history and quality of life, with follow-ups for 5 years. Enrolment started on 2 April 2018, and FENOX will close on 31 March 2028. We will analyse the biological samples using state-of-the-art molecular biology methods and correlate the findings with the medical records and questionnaire data.

**Ethics and dissemination:**

The findings will be published in high-ranking journals in the field and presented at national and international conferences.

**Trial registration number:**

ISRCTN13560263.

Strengths and limitations of this studyFibroids and Endometriosis Oxford (FENOX) combines the study of endometriosis and uterine fibroids to identify the underlying mechanisms of both conditions.The study comprises biological samples as well as comprehensive phenotypic data.World Endometriosis Research Foundation Endometriosis Phenome and Biobanking Harmonisation Project criteria are applied to ensure the best possible standardisation.The longitudinal aspect is an important feature of FENOX, but this depends on uptake and compliance by participants.The control group comprises women undergoing surgery for gynaecological indications other than endometriosis or uterine fibroids; thus, they are not completely healthy controls.

## Introduction

Millions of women suffer from the consequences of endometriosis^1 2^ and uterine fibroids.^3 4^ These include pelvic and abdominal pain, abnormal uterine bleeding, infertility and miscarriages.^5–8^ As such, these conditions affect women and their families in their everyday lives, and have been shown to have an enormous socioeconomic impact on society, in general. In the USA, fibroids are cited to be the cause for over 50% of hysterectomies,^9^ and direct costs for their treatment is estimated between US$4 and US$9 billion.^10^

Clinically relevant, non-invasive diagnostic tests including biomarkers or imaging techniques do not exist for many forms of endometriosis,^11–13^ resulting in an average delay in diagnosis of 8–12 years. Current treatment options are associated with significant side effects and risks and include hormonal suppression/modification, surgical removal or, in the case of fibroids, embolisation and MRI-guided focused ultrasound.

Therefore, there exists a significant unmet clinical need to better understand the underlying mechanisms of these conditions, which will enable us to develop more specific diagnostic tests and will eventually lead to individualised treatment, with fewer side effects and better efficacy. To achieve this goal, it is essential to collect prospective high-quality, standardised clinical and intraoperative data and corresponding biological samples. Our group has been at the forefront of the development of standard operating procedures and questionnaires for endometriosis as part of the World Endometriosis Research Foundation’s (WERF) Endometriosis Phenome and Biobanking Harmonisation Project (EPHect),^14–17^ and we are planning to establish similar standards in uterine fibroid research.

In the Fibroids and Endometriosis Oxford (FENOX) study, we aim to improve our understanding of the underlying mechanisms of endometriosis and uterine fibroids and their associated symptoms by means of longitudinal observation and laboratory analyses. To achieve this, samples and clinical data will be collected from women undergoing surgery. These samples will be used in state-of-the-art biomedical assays (see section ‘Assays’) to improve our understanding of the underlying biology of these symptoms in women with endometriosis and/or fibroids, which will lead to a better understanding of the conditions, stratification of patient groups and tailored therapies and the development of novel drug targets and biomarkers for diagnosis and treatment.

### Objectives

#### Primary objective

To identify the underlying mechanisms of endometriosis and uterine fibroids and their associated symptoms to improve the outcome of affected women.

#### Secondary objectives

To identify novel biomarkers of endometriosis.To identify clinical subgroups of endometriosis and uterine fibroids.To understand the genetics underlying these conditions and explore the relevant downstream molecular pathways.To investigate the relation between the presence of fibroids and the symptoms, for example, abnormal uterine bleeding.To identify novel drug targets.To develop models of disease progression and prediction.To investigate conditions or symptoms associated with endometriosis and/or uterine fibroids, including: symptoms and characteristics of the female reproductive system (characteristics of menstrual bleeding, fertility, infertility, pregnancy outcomes), pelvic as well as non-pelvic pain conditions, metabolic phenotypes (polycystic ovarian syndrome, obesity and fat distribution), cardiovascular conditions and symptoms, neuroangiogenesis and related neurological symptoms, immunological disorders and cancers.

### Outcomes

#### Primary outcome

We will used questionnaire data, medical records and sample analysis to investigate the genetic and molecular basis of the pathogenesis and symptoms of endometriosis and uterine fibroids. At the end of the recruiting period, that is, from December 2022 onwards, the collected data and samples will be analysed and compared between endometriosis/fibroid cases and non-affected controls.

#### Secondary outcomes

Prospective standardised questionnaires and samples will be collected according to EPHect standards. The correlation of cellular, molecular and genetic data and endometriosis status will allow us to define novel biomarkers of the disease.

Clinical notes and questionnaires in combination with sample data will be used to define clinical subgroups of patients.

The molecular and genetic findings will be compared against public databases of disease-relevant molecular pathways, and in vitro experiments will be carried out to test hypothetical connections between the genetics and manifestation of disease.

The blood vessels and endothelial cells will be compared between tissue from women presenting with fibroids and those without.

The detailed comparison between tissue from women with fibroids and those without will yield differences in terms of proteins expressed; these can then be tested as targets using known or new drugs.

As data accumulate and genetic mechanisms become clear, hypotheses will be formed as to the likely progression of disease. These will be tested against the reports from the follow-up questionnaires.

We will use questionnaire data, medical records and sample analysis to investigate the genetic and molecular basis of the pathogenesis and symptoms of conditions or symptoms associated with endometriosis and/or uterine fibroids.

## Methods and analysis

### Study design

FENOX is a prospective study that aims to improve our understanding of the underlying mechanisms of endometriosis and uterine fibroids and their associated symptoms by means of longitudinal observation and laboratory analyses. Biological samples such as blood, saliva, urine, fat, peritoneal fluid and—if found—endometriosis tissue or fibroids as well as detailed clinical and intraoperative data will be collected from women of reproductive age with and without endometriosis-associated and fibroid-associated symptoms, such as pain, abnormal uterine bleeding and infertility. Women undergoing surgery for these conditions, and women undergoing surgery for unrelated gynaecological conditions as part of their normal clinical management will be asked to participate (figure 1). An incidental diagnosis of endometriosis or uterine fibroids will lead to the patients’ inclusion into the relevant case groups. All women attending clinics receive a letter informing them of ongoing research, and eligible women will be identified initially by research nurses or clinical staff during clinic visits. Once a woman has expressed an interest in participating in this study, they will be consented by a member of the research team (figure 2).

**Figure 1 F1:**
[figure not shown]
Participant groups and procedures. The participants will be allocated into case or control groups and tissues will be sourced according to the course of clinical intervention: Participants with fibroids treated by transcervical resection (TCRF) will not undergo abdominal surgery, while abdominal surgery is necessary if the fibroids are treated by laparoscopy, open myomectomy or hysterectomy. In these cases, peritoneal fluid can be obtained in addition to the tissue samples (fibroid, myometrium, endometrium). Endometriosis patients will undergo laparoscopy. If found without endometriosis, they will be grouped with the controls, who are women undergoing surgery for other, unrelated conditions (eg, tubular ligation).

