### Exclusion criteria

The participant may not enter the study if ANY of the following apply:

Women who are pregnant.Women who are unable to read, or to understand written or spoken English.History of cancer/diagnosis of current cancer.

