### Study settings

#### Baseline assessments

Consented participants will be asked by the research team to complete a baseline questionnaire before their surgery. This may be sent to them for example, via mail or email before surgery or given to them in paper form in the clinic. Alternatively, participants have the option to complete an online version of the questionnaire or they may fill in the questionnaire on their handheld device. Each participant will receive a unique login for the online questionnaires.

The questionnaire data will be withheld from the research team until written informed consent is obtained and will be destroyed if this is not granted.

All participants will be sent further questionnaires at different time points (approximately 6–8 weeks, 6 months, 12 months and then yearly for 5 years after surgery). Participants may be reminded (twice, maximally) to return completed questionnaires via mail, email, phone or text or similar.

On the day of surgery, they will be asked to provide a mid-stream urine and a saliva sample. In addition, blood will be collected by peripheral venepuncture. The procedures will be explained to the women again and they will be given the opportunity to ask questions. Assessment of the presence and extent of disease will be performed by the operating surgeon.

Samples that may be taken at time of surgical procedures are as follows:

*Laparoscopy for suspected endometriosis*: endometrial biopsy, peritoneal fluid aspiration, fat tissue biopsy, endometriotic tissue if present, peritoneal biopsy.*Laparoscopy for uterine fibroids*: endometrial biopsy, peritoneal fluid aspiration, fat tissue biopsy, endometriotic tissue (if present), peritoneal biopsy, fibroid tissue, myometrial biopsy.*Laparotomy for uterine fibroids*: endometrial biopsy, peritoneal fluid aspiration, fat tissue biopsy, endometriotic tissue if present, peritoneal biopsy, fibroid tissue, myometrial biopsy.*Transcervical resection of uterine fibroids*: endometrial biopsy, fibroid tissue, myometrial biopsy.*Laparoscopy for tubal sterilisation (controls)*: endometrial biopsy, peritoneal fluid aspiration, fat tissue biopsy, peritoneal biopsy, myometrial biopsy.*Hysterectomy*: whole uterus as excess tissue from women with fibroids as well as from controls without fibroids, who undergo surgery for other indications (such as heavy menstrual bleeding, or pain), peritoneal fluid aspiration, fat tissue biopsy and peritoneal biopsy.

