### The number of participants

It is now recognised that both endometriosis and uterine fibroids are very heterogeneous conditions. Our previous studies^22 23^ and systematic reviews^24 25^ have clearly identified a lack of sufficiently powered studies. Multiple large-scale research collaborations are currently in place investigating different aspects of endometriosis,^26^ and we plan similar efforts for uterine fibroids. Therefore, large patient numbers are needed.

The Endometriosis CaRe Centre at Oxford is the UK’s largest endometriosis centre. Similarly, as a tertiary referral centre, we see many women with fibroid-associated symptoms. As a result, we have the unique opportunity to collect large amounts of data and samples, which is essential to produce clinically meaningful outputs. Given our current patient recruitment rate (endometriosis: 100/year, uterine fibroids, 200/year), we estimate an enrolment of approximately 2×1200 women over the course of the study (800 endometriosis patients+400 non-endometriotic controls, 800 fibroid patients+400 non-fibroid controls). Fibroids already collected as excess tissue under the Oxford Radcliffe Biobank (REC Ref 09/H0606/5+5) will also be included in this study, currently approximately 70 samples.

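### An endometriosis patient with a negative index laparoscopy becomes a control whatever her history, so previously confirmed disease can sit among the controls and dilute germline and persistent-marker comparisons

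*Protocol article*

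**What the plan says.** The grouping rule for the endometriosis arm stands in the caption of Figure 1. It begins "Endometriosis patients will undergo laparoscopy" and goes on: "If found without endometriosis, they will be grouped with the controls, who are women undergoing surgery for other, unrelated conditions (eg, tubular ligation". It is not limited to a first or diagnostic laparoscopy.

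Two other rules also turn on the finding at the index operation:
- Baseline assessments: "Assessment of the presence and extent of disease will be performed by the operating surgeon".
- Study design: "An incidental diagnosis of endometriosis or uterine fibroids will lead to the patients’ inclusion into the relevant case groups".

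Two places describe controls differently, by indication for surgery. The Strengths and limitations list says "The control group comprises women undergoing surgery for gynaecological indications other than endometriosis or uterine fibroids". The Participants section plans 800 women with the condition and 400 operated on for other reasons in each disease arm.

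The exclusion criteria read "Women who are pregnant.Women who are unable to read, or to understand written or spoken English.History of cancer/diagnosis of current cancer". Neither they nor the inclusion criteria mention earlier endometriosis.

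**The concern.** Recruitment is at a specialist site: "The Endometriosis CaRe Centre at Oxford is the UK’s largest endometriosis centre". The Introduction names surgical removal and hormonal suppression as current treatments. It is therefore plausible that some women come to the index laparoscopy with a confirmed diagnosis behind them and no lesion visible that day. The caption then labels known disease as absent.

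This bears on a stated secondary objective: "To understand the genetics underlying these conditions and explore the relevant downstream molecular pathways". Germline genotype does not change when a lesion is excised, so for that analysis such a woman is a case counted as a control. The contrast shrinks towards zero, and a larger sample does not remove the bias. The same holds for any blood or tissue marker that persists after excision. In a biomarker analysis, a true signal in these women would also count as a false positive and lower the apparent specificity.

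**Working it through.** **Does anything in the article offset the rule?**
- Data analysis plan: the sensitivity analysis covers only women with both endometriosis and fibroids.
- Analysis of outcome measures: matching is conditional on influential differences such as body mass index or comorbidities. Matching does not correct a wrong case label.
- Questionnaires and Medical records: history is collected, but no section uses it to assign groups.

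Nothing offsets it.

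**The plan's own figures.** The Power calculations section reproduces. For r = 0.3, n is 84.07, which rounds up to 85. For the 15-group ANOVA with f = 0.2, n is 31.36 per group, which rounds up to 32, and 15 × 32 = 480. These figures make no allowance for mislabelled controls, but they are correct on their own inputs and this point does not change them.

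**Size of the dilution.** Let c be the share of all endometriosis controls who have earlier confirmed disease. A persisting mean or allele-frequency difference is multiplied by (1 − c), and information by about (1 − c)². The loss is 1 − 0.9² = 19% at c = 10% and 1 − 0.8² = 36% at c = 20%.

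Inputs for a germline example:
- From the article: 800 cases and 400 controls, that is 1600 and 800 alleles.
- Assumed: control allele frequency 0.30, true odds ratio 1.3, one two-sided test at 0.05, and c from 0 to 20%.

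Steps:
1. Case odds are 1.3 × 0.30/0.70 = 0.557, so the case frequency is p1 = 0.557/1.557 = 0.358.
2. The mixed control frequency is pc = (1 − c) × 0.30 + c × 0.358.
3. SE = √[p1(1 − p1)/1600 + pc(1 − pc)/800], and power = Φ((p1 − pc)/SE − 1.96).
4. At c = 0: difference 0.0578, SE 0.0202, ratio 2.868, power Φ(0.908) = 0.818.
5. At c = 10%: pc = 0.3058, difference 0.0520, SE 0.0202, ratio 2.572, power Φ(0.612) = 0.730.

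For the repaired grouping, the 400c women move to the cases and are not replaced. At c = 10% this gives 840 cases v 360 controls (1680 v 720 alleles), SE 0.0207, ratio 2.792 and power 0.797.

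| c | women among 400 controls | odds ratio seen | power as written | power with these women as cases |
|---|---|---|---|---|
| 0 | 0 | 1.300 | 0.818 | 0.818 |
| 2% | 8 | 1.293 | 0.802 | 0.814 |
| 5% | 20 | 1.282 | 0.776 | 0.809 |
| 10% | 40 | 1.265 | 0.730 | 0.797 |
| 20% | 80 | 1.231 | 0.625 | 0.770 |

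A continuous marker that persists behaves alike. With an assumed standardised difference of 0.2 and 800 v 400 women, power is 0.904, 0.873, 0.836 and 0.743 at c = 0, 5, 10 and 20%.

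**The case against.** **It is a figure caption in a condensed article.** The full protocol may define control status more closely. Baseline assessments speaks of laparoscopy for suspected endometriosis, and the number-of-participants section calls the comparison group non-endometriotic. On that reading the caption means only women with suspected disease in whom none is found. This has force: the article nowhere says that a previously confirmed case must become a control. But the caption states a rule and attaches no history condition to it, and the article's own descriptions of controls disagree. That can be judged as printed.

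**The share is unknown and may be small.** This stands. Moreover, c is a share of all controls, including those from sterilisation and hysterectomy. To reach 10%, for example, half of the controls would have to be negative laparoscopies and 20% of those would need earlier confirmed disease (0.5 × 0.2 = 0.10). Nothing in the article supports 10% or 20% in particular, and at 2% the loss is under two points.

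**It can be put right at analysis.** This is largely true. Samples are stored, history is collected and the study is exploratory. That makes the repair cheap, but no section commits to it.

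**Stronger readings to resist.**
- A reader might infer that every case-control contrast is diluted. For a marker that depends on lesions now present, a woman whose lesions were removed may be a proper lesion-free comparator.
- A reader might extend the point to women with earlier fibroid treatment. The caption's rule concerns endometriosis patients having laparoscopy, and no sentence sends treated fibroid patients to the controls.
- A reader might take the full 82% as recoverable. It is not, because the repair removes controls.

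**Conclusion.** The point holds for the endometriosis arm, and for germline comparisons and markers that persist after excision. The direction, towards zero, follows from the rule as written wherever such women are present. The size cannot be found from the article. On the stated assumptions the loss of power is about 2, 4, 9 and 19 points at c = 2, 5, 10 and 20%, of which regrouping recovers about 1, 3, 7 and 14. The planned Bonferroni correction would put absolute power below these single-test values. Separately from the size, the caption and the two indication-based descriptions of controls cannot all stand and need to be reconciled.

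**What to change.** Reconcile the Figure 1 caption, the Strengths and limitations list and the Participants section with one definition: an endometriosis control has no endometriosis at the index surgery and no previous surgical or histological diagnosis of it in the questionnaire or medical records.

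Put women with previous but no current disease in a separate group. Count them as cases in germline analyses and leave them out of the controls for tissue and biomarker analyses. For lesion-dependent markers, add a sensitivity analysis that brings them back as lesion-free comparators. Report their number, so that c becomes known.

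The cost is one grouping rule, one derived variable and somewhat fewer controls. No new procedure is needed. One check comes first: the abstract says that medical history is collected, but the Questionnaires and Medical records sections do not name earlier surgery or histology, so confirm that these items are captured.

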**Figure 2 F2:**
[figure not shown]
Flow chart of participant data and tissue sampling. Consented participants of the different arms of the study donate pre-operative samples and fill in a baseline questionnaire. They can donate a range of tissue samples according to their condition and treatment mode (eg, fibroids or endometriotic tissue, peritoneal fluid), and are asked to repeatedly fill in follow-up questionnaires on their condition and quality of life, so that the clinical findings can be correlated with the outcome years later.

Blood, saliva and urine will be taken prior to surgery. Tissue and peritoneal fluid (where applicable) will be taken at the time of the scheduled surgery.

In order to determine the effect of the surgical removal of the fibroids on the local tissue, it is necessary to take an additional endometrial biopsy after the planned surgical intervention. This sample will be timed to synch with the same time point in the menstrual cycle that the original sample was taken, and thus will give us a unique insight into the biology of the conditions. During this visit, blood and urine samples will be taken again also. Women can opt in or out of the additional clinic visit where these samples would be taken.

Women will be asked to complete questionnaires on paper, online or into their electronic handheld devices (health, pain, medication and, initially, ethnicity) at different time points. There will be a lengthy questionnaire at baseline before surgery (taking an estimated 45 min to complete), and shorter versions (taking up to 30 min to complete) postoperatively at 6–8 weeks, 6 months, 12 months and thereafter yearly for a total of 5 years after surgical intervention.

